#### 9.4.2 SERIOUS ADVERSE EVENT REPORTING

The SI will complete a SAE Form within the following time frame:

- All SAEs will be recorded on the SAE Form and submitted by the site PI to the Overall study PI/Sponsor within 48 hours of initial receipt of the information (weekends and holidays are not included) and addressed to:  
[name] [name]  
Study Medical Monitor  
International Vaccine Institute  
[name],  
[name],  
[contact]  
[contact]  
[contact]  
[contact]
- PFDA to be notified within 7 calendar days (for death and life threatening cases) and 15 calendar days [for those SAE which are fulfilling the criteria of Suspected Unexpected Serious Adverse Reactions (SUSAR)] by the sponsor/overall study PI/ Designee within the awareness of and the rest of the SAEs can be reported with the annual report.

All information (which may include special investigations and treatment received) will be recorded on the SAE Form and submitted to PFDA and site specific IRB. All SAEs will be followed until satisfactory resolution or until the site investigator deems the event to be chronic or to be stable. Other supporting documentation of the event may be requested by the sponsor and should be provided as soon as possible. SAE reporting to IVI IRB on regular basis is not mandatory (except those are of SUSAR category) and will be reported with the annual renewal report.

- The sponsor will be responsible for notifying the IVI IRB of Suspected Unexpected Serious Adverse Reactions (SUSAR) within 24 hours of initial receipt of the information (weekends and holidays are not included)

The SUSAR report will include the following information:

- It is mandatory to include an identifiable patient, an identifiable reporter, a suspect drug, and an adverse event
- Protocol information: protocol number and date
- A detailed description of the event, incident, experience, or outcome
- An explanation of the basis for determining that the event, incident, experience, or outcome represents an unexpected problem

---

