| Protocol Number: IVI T004                                                                                                                                                                                                                                                                                                                                                                                                                                                                                                                                                                                                                                                                           |                                  |
| Study Sites: Study participants may be enrolled from the following sites; 
 
• University of the Philippines Manila - National Institutes of Health, Ermita Manila
 
• Lingga Health Research Center Calamba, Laguna
 
• Putatan Research Center, Putatan, Muntinlupa City
 
• Magcase Health Center, San Pablo City, Laguna
 
                                                                                                                                                                                                                                                                                                    |                                  |
| Study Period (years/months)

Estimated date first participant enrolled: Jan 2020
Estimated date last participant enrolled: May 2020
Estimated duration of the trial: 18 months                                                                                                                                                                                                                                                                                                                                                                                                                                                                                                          | Phase of development: III |

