#### 9.1.2 DEFINITION OF SERIOUS ADVERSE EVENTS (SAE)

An AE or suspected adverse reaction is considered "serious" if, in the view of either the investigator or sponsor, it results in any of the following outcomes:

- Results in death
- Life-threatening event
- Requires in-patient hospitalization > 24 hours or prolongation of existing hospitalization
- Results in persistent or significant incapacity or substantial disruption of the ability to conduct normal life functions
- Congenital anomaly/birth defect
- Important medical events that may not result in death, be life-threatening, or require hospitalization may be considered serious when, based upon appropriate medical judgment, they may jeopardize the participant and may require medical or surgical intervention to prevent one of the outcomes listed in this definition.

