#### 9.4.3 SAFETY OVERSIGHT

An internal Safety Monitoring Committee (SMC) will be responsible to oversee the vaccine safety patterns during the course of the clinical trial. The SMC will be composed of individuals with appropriate expertise, including at least one pediatrician. The SMC will review blinded safety data on a regular basis according to the guidelines of the SMC charter. The SMC will send a summary of safety review findings to the site PIs and the Study Medical Monitor.

An independent Data Safety Monitoring Board (DSMB) will be constituted of experts from various fields of Medicine external to sponsor's organization. The DSMB will oversee the study in terms of safety data as per DSMB charter. DSMB will have the authority to halt or terminate the study in case of any safety signals. DSMB chair will issue a recommendation letter after each meeting.

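### Section 9.4.2 counts the 48-hour SAE report in working time even for deaths, which permits 4 calendar days over an ordinary weekend, and it never finishes saying when the regulator's clock starts

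*Protocol*

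**What the plan says.** Section 9.4.2 of the protocol sets one limit for the first step of SAE reporting. "All SAEs will be recorded on the SAE Form and submitted by the site PI to the Overall study PI/Sponsor" is the duty, and the time allowed is "within 48 hours of initial receipt of the information (weekends and holidays are not included"). Section 9.1.2 lists "Results in death" as the first outcome that makes an event serious, followed by life-threatening events, so both fall under this limit. No shorter site-to-sponsor time is given for them.

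The next item in 9.4.2 concerns the Philippine regulator (PFDA): "PFDA to be notified within 7 calendar days (for death and life threatening cases) and 15 calendar days", the latter for SUSARs. The notifier is named as the sponsor, the overall study PI or a designee. The words that should say when the period starts read "within the awareness of and the rest of the SAEs can be reported with the annual report". The object of the awareness is missing.

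The sponsor's SUSAR notice to its own IRB has a 24-hour limit, again without weekends and holidays. On oversight, section 9.4.3 states that the "DSMB will have the authority to halt or terminate the study in case of any safety signals".

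**The concern.** Two things in 9.4.2 do not sit well together. The link from site to sponsor runs in working time, while the regulator's periods run in calendar days. A site that follows the rule exactly may hold a report of a death for several calendar days. Because the start of the regulator's period is not stated, the text does not settle whether those days count against the 7 or 15.

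Several steps depend on the sponsor knowing. These are the PFDA notice, the SUSAR notice to the sponsor's IRB (both 9.4.2), and unblinding after a vaccine-related death or life-threatening event, which the sponsor must approve (5.3.3). Each participant receives a single dose, so the exposure at stake is that of other participants while enrolment is open. Up to four sites may enrol, so an event known at one site may bear on vaccination at another. SAEs that come to light after enrolment closes do not raise this issue.

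**Working it through.** The protocol states no derived figure on this point, so there is none to reproduce. The check is calendar arithmetic.

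**Inputs**
- Counted time allowed: 48 hours (9.4.2).
- Days not counted: weekends and holidays (9.4.2).
- Regulator periods: 7 calendar days for fatal and life-threatening events, 15 for SUSARs (9.4.2).
- Holidays adjoining a weekend: not in the protocol; 0, 1 and 2 are assumed.

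**Formula.** Longest permitted time = 48 h + 24 h × (whole excluded days that fall before the 48 counted hours are used up).

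| Case | Calculation | Calendar days |
|---|---|---|
| Mid-week, nothing excluded | 48 h | 2 |
| Ordinary weekend | 48 + 2 × 24 = 96 h | 4 |
| Weekend plus one holiday (assumed) | 48 + 3 × 24 = 120 h | 5 |
| Weekend plus two holidays (assumed) | 48 + 4 × 24 = 144 h | 6 |

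Worked example for the ordinary weekend: the site learns of the event on Friday at 17:00. It uses 7 h on Friday, none on Saturday or Sunday, 24 h on Monday and 17 h on Tuesday. 7 + 24 + 17 = 48, so the report is due on Tuesday at 17:00, 96 clock hours later.

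**How often the exclusion matters in a week without holidays.** Take receipt at each of the 168 hours of the week. The permitted time exceeds 2 days for 23 hours on Thursday and for all 24 on each of Friday, Saturday and Sunday: (23 + 72)/168 = 95/168, about 57%. The sum of permitted times is 144 (Monday to Wednesday, 72 × 2) + 94 (Thursday, 1 × 2 + 23 × 4) + 96 (Friday, 24 × 4) + 84.5 (Saturday) + 60.5 (Sunday) = 479 days. The mean is 479/168 = 2.85 days. This treats all hours of receipt as equally likely.

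**Interaction with the regulator's periods**
- If the period starts at site awareness, a delay of 4, 5 or 6 days leaves 3, 2 or 1 of the 7 days, and 11, 10 or 9 of the 15.
- If it starts at the notifier's awareness, the 7 and 15 days are intact. The total from site to regulator can then reach 7 + 4 = 11 to 7 + 6 = 13 days, or 15 + 4 = 19 to 15 + 6 = 21 days.

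**After the fix.** With 48 clock hours, Friday 17:00 leads to Sunday 17:00. The maximum is 2 calendar days in every case.

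**The case against.** The 48 hours is an outer limit for submitting a form, not a measure of when the sponsor learns of an event. Section 9.4.1 asks for prompt eCRF entry, lets site investigators consult the medical monitor as needed, and refers reporting details to the manual of procedures, which is not shown. That stands as mitigation. None of these provisions in the protocol has a time limit, so they do not replace one.

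A reader might infer that vaccination must go on for days with nobody able to stop it. The protocol does not support this. Under section 7.11 the regulator, site IRBs, the DSMB and the safety monitoring committee may each instruct suspension, and the PI may recommend it after consulting the sponsor. Nothing there requires waiting for the 48 hours to run out.

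A reader might also turn the delay into a number of further vaccinations, using the planned pace from January 2020 to "Estimated date last participant enrolled: May 2020". That is not a sound measure either. Section 5.2 reports that the lockdown from 13 March 2020 disrupted enrolment. Any count over two working days would also be the same for a report received on a Monday, when the exclusion plays no part.

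Finally, working time for sites and calendar days for the notifier are duties of different parties and do not contradict each other. That is right. Counting a site's report of a death in working time is a design choice, open to criticism for the delay it permits, not an internal inconsistency. The incomplete regulator sentence is a plain drafting defect.

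**Conclusion.** The point holds in a limited form. As written, 9.4.2 permits 4 calendar days between a site's knowledge of a death or life-threatening event and the sponsor's report whenever an ordinary weekend intervenes. That figure needs no outside assumption. The 5- and 6-day figures need one or two adjoining holidays. All of these are permitted maxima, not expected delays.

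A reader might infer that up to 6 of the regulator's 7 days are lost. That would require two adjoining holidays and a period that starts at site awareness. The sentence names the sponsor, overall study PI or designee as notifier, and that party's awareness is the natural reading, under which the 7 days are not eroded. The protocol should say so.

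The effect is on the speed of safety reporting while enrolment is open. No estimate, power figure or analysis is affected.

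**What to change.** In section 9.4.2:
1. Delete the weekend and holiday exclusion from the site-to-sponsor SAE report, at minimum for fatal and life-threatening SAEs, so that the existing 48 hours are clock hours.
2. Complete the PFDA sentence so that it states whose awareness starts the 7- and 15-day periods. The natural completion is the notifier already named there: the sponsor, overall study PI or designee.

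The cost is a small wording amendment and a memo to sites, and for a few events an initial report sent outside office hours. No treatment, dose or stopping rule changes.

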#### 9.4.3 SAFETY OVERSIGHT

An internal Safety Monitoring Committee (SMC) will be responsible to oversee the vaccine safety patterns during the course of the clinical trial. The SMC will be composed of individuals with appropriate expertise, including at least one pediatrician. The SMC will review blinded safety data on a regular basis according to the guidelines of the SMC charter. The SMC will send a summary of safety review findings to the site PIs and the Study Medical Monitor.

An independent Data Safety Monitoring Board (DSMB) will be constituted of experts from various fields of Medicine external to sponsor's organization. The DSMB will oversee the study in terms of safety data as per DSMB charter. DSMB will have the authority to halt or terminate the study in case of any safety signals. DSMB chair will issue a recommendation letter after each meeting.

## 10 STUDY MONITORING

Study monitoring and auditing will be performed in accordance with the sponsor's procedures, GCP guidelines and any other applicable regulatory requirements.

Upon successful approval of the protocol and establishment of the Regulatory File, the clinical monitor will establish a clinical monitoring plan (CMP). To ensure that the investigator and the study staff understand and accept their defined responsibilities, the clinical monitor will maintain regular correspondence with the site and may be present during the course of the study to verify the acceptability of the facilities, compliance with the investigational plan and relevant regulations, and the maintenance of complete records.

Investigators and/or their study staff will be trained on the study protocol and all applicable study procedures prior to study initiation. Electronic CRFs supplied by the sponsor must be completed for each enrolled participant. The data entries as well as study related documents will be checked by the sponsor and/or trained delegates of the sponsor.

Study progress will be monitored by IVI study team or representative (e.g., a contract research organization) as frequently as necessary to ensure the rights and well-being of study participants are protected; to verify adequate, accurate and complete data collection; protocol compliance and to determine that the study is being conducted in conformance with applicable regulatory requirements. Arrangements for monitoring visits will be made in advance in accordance with the monitoring plan, except in case of emergency.

## 11 STATISTICAL CONSIDERATIONS

### 11.1 SAMPLE SIZE

A total of 1800 participants (1500 in Vi-DT test arm and 300 in control arm) aged 6 months to 45 years will be enrolled in this study. Participants will be randomized equally into first 2 groups of 750 participants each and third group with 300 participants within each age strata of 6 months to less than 2 years, 2 to less than 18 years and 18 to 45 years.

The sample size of two Vi-DT groups is decided based for the immunogenicity equivalence and safety data requirements. The immunogenicity subset in adult participants, N=250 per group,

will provide 94% power to show equivalence of geometric mean titres (GMT) of anti-Vi IgG at 4 weeks (28 days) after vaccination of Vi-DT (MD) and Vi-DT (SD) , with the equivalence margin of [0.67, 1.5] (WHO TRS 924). Coefficient of variation (CV) of immunogenicity titre is conservatively assumed as 2.0 based on IVI T001 and T002 studies at type 1 error rate of 0.05, and 10% drop out rate is also assumed. This sample size of N=250 will provide 95% power, for equivalence tests of seroconversion rate between two formulations of Vi-DT with equivalence margin of [-10%, 10%]. In this calculation, 90% of sero-conversion rate in Vi-DT is assumed (based on IVI T001) with type 1 error rate of 0.05. The sample size of N=300 control (Meningococcal vaccine) is calculated to observe at least one events with 1% of the upper limit of 95% CI for any adverse event of incidence according to rule of three.

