## **Statistical Considerations**

The sample size of two Vi-DT groups is decided based on the immunogenicity equivalence and safety data requirement. The immunogenicity subset in adult participants, N=250 per group, will provide 94% power to show equivalence of geometric mean titres (GMT) of anti-Vi IgG at 4 weeks (28 days) after vaccination of Vi-DT(MD) and Vi-DT (SD), with the equivalence margin of 0.67 to 1.5 following WHO recommendation per (WHO TRS 924). Coefficient of variation (CV) of immunogenicity titre is conservatively assumed as 2.0 based on data from IVI T001 (i.e., Vi-DT phase 1 in children, adolescents, and adults in the Philippines) and IVI T002 (i.e., Vi-DT Phase 2 in infants/toddlers in the Philippines) studies with type 1 error rate of 0.05 and 10% drop out rate are also assumed. This sample size of N=250 will provide 95% power, for equivalence tests of seroconversion rate between two formulations of Vi-DT with equivalence margin of [-10%, 10%]. In this calculation, 90% of sero-conversion rate in Vi-DT is assumed (based on IVI T001) with type 1 error rate of 0.05. The sample size of N=300 control (Meningococcal vaccine) is calculated to observe at least one events with 1% of the upper limit of 95% CI for any adverse event of incidence according to rule of three.

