## 5.2 METHODOLOGY

This is a multicenter, randomized, observer-blinded, controlled, immune equivalence study of a multi-dose formulation with 2PE preservative of SK bioscience Vi-DT (MD) compared to single dose formulation without preservative of SK bioscience Vi-DT (SD) in participant (6 months - 45 years) including safety population. The Vi-DT vaccines will be administered to 1,500 healthy participants of 6 months to 45 years of age and followed up for 24 weeks after the injection for safety. Adult participants (N=500) will be followed up additionally for immunogenicity 4 weeks post vaccination and all participants till 24 weeks for safety post single dose of the MD & SD formulations. 300 healthy participants will be given control vaccine (Meningococcal conjugate Vaccine) to check the background safety events. The primary objective is to demonstrate the equivalence of immunogenicity as measured by anti-Vi IgG GMT titer 4 weeks after a single dose of MD/SD formulation in adults. The secondary objective is to demonstrate the equivalence of immunogenicity in terms of seroconversion rates as measured by anti-Vi IgG ELISA antibody titers, 4 weeks after a single dose of MD/SD formulations in adults. A descriptive evaluation of safety at 4 and 24 weeks post single dose of (MD/SD/ Meningococcal conjugate Vaccine ) will be performed. The Vi-DT vaccine from both MD & SD formulations will be administered as a single dose of 25 µg.

Eligible participants enrolled into the study will be randomized into one of the three study groups within each age stratum of 6 months to less than 2 years, 2 to less than 18 years, and 18 to 45 years. Participants will be observed at the study site for 30 minutes after vaccination for immediate safety assessment. Solicited adverse events will be recorded on a diary card during 7 days after vaccination. Unsolicited adverse events will be recorded during the 4 weeks after vaccination. Serious adverse events will be recorded during the entire study period. With the exception of designated study site personnel responsible for vaccine administration, study

investigators, study nurses, and those assessing clinical outcomes, and data analysts will be blinded to vaccine allocation until database lock for the final analysis.

Blood samples will be collected at baseline prior to vaccination and at 4 weeks post vaccination from adult participants (18-45 years) only for immunogenicity assessment.

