**Table 1. Immunization Schedule**

| Group of Vaccinees and age group                      | Age Strata  | N*  | D0                     |
|-------------------------------------------------------|-------------|-----|------------------------|
| Group A
750 participants
(6 mo - 45 yrs) | 18-45 yrs   | 250 | (25 µg 0.5 mL)         |
|                                                       | 2- <18 yrs  | 250 | (Vi-DT)                |
|                                                       | 6 mo-<2 yrs | 250 | Multi dose formulation |

|                                                       |             |     |                                                      |
|-------------------------------------------------------|-------------|-----|------------------------------------------------------|
| Group B
750 participants
(6 mo - 45 yrs) | 18-45 yrs   | 250 | (25 µg 0.5 mL)
(Vi-DT)
Single dose formulation |
|                                                       | 2- <18 yrs  | 250 |                                                      |
|                                                       | 6 mo-<2 yrs | 250 |                                                      |
| Group C
300 participants
(6 mo - 45 yrs) | 18-45 yrs   | 100 | Control
(Meningococcal
Conjugate vaccine)      |
|                                                       | 2- <18 yrs  | 100 |                                                      |
|                                                       | 6 mo-<2 yrs | 100 |                                                      |

\* Age Strata wise number of enrolled subjects may be adjusted during the actual enrollment.

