# Phone calls on Day 3 will be arranged after vaccine administration to ensure completion of the Participant's DC and to check their health status. No deviation will be considered if the phone call could not be completed on the exact date.

@ Only from Adult subjects of 18 to 45 years

\* After visit 4, only concomitant medication related to SAE will be captured

\$ Blood pressure collection is for adult population of 18 years to 45 years

% Urine pregnancy test (UPT) will be performed to all female participants of childbearing age from menarche.

© During city lock down only safety follow up has been done through phone call in V3 and V4. Even the post vaccination blood sample at V4 could not be collected.

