### **Age Strata reassignment (Stratawise Enrollment number of subject)**

The initial enrollment plan required an equal number of subject enrollment from each age stratum and the current plan allows for the adjustment of the required number of subjects in each stratum during the enrollment period.

Post-dose blood sample could not be collected from the enrolled adults stratum due to COVID-19. As of 13MAR2020, the Philippines government has imposed a country-wide lock down (as a result of the COVID-19 pandemic) which has impacted the ongoing activities for the clinical trial. Subjects enrollment as well as planned visit 4 blood collection (the post-vaccination blood

sample from adults stratum) has been impacted because of the lockdown. In this situation, there will be additional subjects enrollment into the adults stratum so as to keep the initial planned statistical power for immune equivalence test as planned initially, while reducing the enrollment of subjects in the other two age strata. This will ensure the total number of subjects at 1800 as per original plan.

Due to city lock down those subjects whose blood sample could not be collected on V4, their post- vaccination blood sample would not be collected when lock down is lifted. This will be considered as deviation and will be informed to respective ethics committee.

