#### 11.4 ANALYSIS DATASETS

The Full Analysis set (FAS) is a modified intention-to-treat (m-ITT) analysis set that will include all participants randomized in the study who received at least one dose of investigational vaccines. This data set will be used for demographic information and safety analysis.

The immunogenicity analysis set is a subset of FAS of those who is randomized, received at least one dose of investigational vaccines and have at least one post-baseline immunogenicity data available.

The per-protocol (PP) analysis set will be a subset of the immunogenicity analysis set who do not have protocol violations (defined as major deviation from the protocol compromising the scientific integrity of the study) with regards to the inclusion/exclusion criteria, are compliant with study procedures, completed all visits as scheduled and received the correct vaccinations.

The immunogenicity analysis set will be used for the primary analysis of the immunogenicity endpoints. A sensitivity analysis using the PP analysis sets will be conducted for the primary and secondary immunogenicity endpoints.

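### The amendment promises extra adults to keep power after the lockdown but sets no revised target, and Section 11.1 still rests 94% power on 250 adults per Vi-DT arm with 10% dropout

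*Protocol*

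**What the plan says.** **Size and power.** The synopsis (Statistical Considerations) states: "The immunogenicity subset in adult participants, N=250 per group, will provide 94% power to show equivalence". Section 11.1 repeats this for "The immunogenicity subset in adult participants, N=250 per group", with a CV of 2.0, a margin of 0.67 to 1.5, a type 1 error rate of 0.05 and 10% dropout. Section 5.2 says: "Adult participants (N=500) will be followed up additionally for immunogenicity 4 weeks post vaccination". The synopsis allocation table and Table 1 print 250 adults in each Vi-DT arm and 100 in the control arm, under a footnote: "Age Strata wise number of enrolled subjects may be adjusted during the actual enrollment".

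**Lockdown.** A footnote to Table 2 records that visits 3 and 4 were done by telephone for safety only, and adds: "Even the post vaccination blood sample at V4 could not be collected". The synopsis and the age-strata reassignment text after Table 2 say that these samples will not be taken once the lockdown ends. The reassignment text then commits to enrolling additional adults, at the expense of the two younger strata, so that the originally planned power is kept. On the total it says: "This will ensure the total number of subjects at 1800 as per original plan".

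**Analysis.** Section 11.4 limits the immunogenicity analysis set, which is the primary set, to participants who "have at least one post-baseline immunogenicity data available". Section 11.5.1 does not impute missing titres in the main analysis. Multiple imputation is only a sensitivity analysis, used if more than 10% is missing. Sections 11.3 and 11.5.4 declare equivalence if the two-tailed 95% interval for the GMT ratio lies within 0.67 to 1.5.

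**The concern.** The power of the primary test depends on the number of adults with a Day 28 titre. Before the lockdown, enrolled adults less 10% was a fair proxy for that number. It no longer is, because some enrolled adults are already known to have no Day 28 sample and no prospect of one. They count towards enrolment and contribute nothing to the test.

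The amendment was written to deal with this, but it stops at an intention. A reader who needs to know when adult enrolment is complete finds only the old 250 and 500, and a footnote allowing change. Because the total is fixed at 1800, the missing number also decides how many children remain in the age-stratum safety summaries, which are a secondary objective. And since the reassignment text defines its goal as keeping the planned power, it matters whether the printed 94% is itself right for the printed size.

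**Working it through.** **Inputs.** From Section 11.1: 250 adults per Vi-DT arm, CV 2.0, margin 0.67 to 1.5, 10% dropout, stated power 94%. From Sections 11.3 and 11.5.4: two-tailed 95% interval inside the margin, which is 0.025 per side. From Section 5.3.1: allocation 2.5:2.5:1. Assumed, because the protocol does not state it: a true GMT ratio of 1.

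**Formula.** On the natural-log scale:

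- SD = √ln(1 + CV²) = √ln 5 = 1.269
- SE = SD × √(2/n), with n analysed per arm
- Power = Φ(ln 1.5/SE − z) + Φ(−ln 0.67/SE − z) − 1, with ln 1.5 = 0.4055 and −ln 0.67 = 0.4005
- z = 1.960 for the written 95% interval; z = 1.645 for 0.05 per side (a 90% interval)

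**Reproducing the 94%.** With n = 250, SE = 1.269 × √(2/250) = 0.1135. The two ratios are 3.573 and 3.529.

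- At z = 1.645: 0.973 + 0.970 − 1 = 0.943. This matches the stated figure.
- At z = 1.960: 0.947 + 0.942 − 1 = 0.888.

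So the printed equivalence power is recovered with 250 *analysed* per arm and 0.05 per side. It is not recovered with the written interval rule, and not after the stated dropout.

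**After the stated 10% dropout.** 250 × 0.9 = 225. SE = 1.269 × √(2/225) = 0.1196. The ratios are 3.390 and 3.348.

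- At z = 1.960: 0.924 + 0.917 − 1 = 0.841.
- At z = 1.645: 0.960 + 0.956 − 1 = 0.915.

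**Power by number analysed per arm.**

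| Analysed per arm | Written 95% interval | 0.05 per side |
|---|---|---|
| 200 | 78% | 87% |
| 225 | 84% | 91.5% |
| 247 | 88% | 94% |
| 250 | 89% | 94% |
| 293 | 94% | 97% |

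A t-based calculation gave results within 0.3 points of these at the sizes checked (225 to 250).

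**Enrolment for 94%, before any lockdown loss.** With 10% dropout: 293/0.9 = 326 per arm under the written rule, or 247/0.9 = 275 per arm at 0.05 per side. If L adults per arm were lost to the lockdown, L is added to either figure. The protocol does not give L.

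**Putting the texts together.** An adult with no Day 28 sample has no post-baseline titre (Table 2 footnote, reassignment text), is outside the primary set (Section 11.4), and is not imputed into it (Section 11.5.1). The 250 in Section 11.1 carries only the 10% allowance. The reassignment text raises the adult number above 250 without saying to what, and Section 11.1 does not refer to it.

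**The case against.** The strongest reply is that the protocol already handles the matter. The reassignment text is a commitment: additional adults will be enrolled so that the planned power is kept. The footnotes to both allocation tables let the stratum numbers change. This stands. A reader might infer that adult enrolment will end at 250 per arm and that the primary test is therefore underpowered by some definite amount. The documents do not support that. They do not plan to stop at 250, and they do not say how many adults lost their Visit 4 sample. A loss of 10%, 20% or 50% of adults would be a guess. The planned accrual dates are labelled as estimates, and enrolment itself was interrupted, so they give no sound basis for one. The power table above shows how power depends on the number analysed; it does not forecast a shortfall.

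A second reply is that 250 may already mean adults with a usable sample, since Section 11.1 calls them the immunogenicity subset and 94% comes out only with 250 analysed. This is possible, but the same sentence group in Section 11.1 assumes 10% dropout, which points to enrolled adults. The ambiguity is itself a reason to define the number.

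A third is that safety by stratum is descriptive and has no stated precision target for children. This also stands: a smaller child stratum is a cost to display, and breaches no stated requirement. Nor is the transfer of slots unlimited, given the fixed total.

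What remains is that the commitment has no number, and that the sections carrying the number were not brought into line with it.

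**Conclusion.** The point holds as a failure of reconciliation in the current protocol. The amended enrolment text raises the adult stratum to protect power. Section 11.1, the synopsis, Section 5.2 and the allocation tables still give the pre-lockdown size, no revised target is stated, and the unit in which the size is expressed no longer matches what the primary analysis uses.

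Separately from the lockdown, the printed power does not follow from the printed inputs. Under the written 95% interval rule, 250 less 10% gives about 84%, and 94% needs about 293 analysed per arm. At 0.05 per side the figures are 91.5% and about 247. All rest on CV 2.0, log-normal titres and a true ratio of 1. A true ratio of 1.05 would lower the 84% to about 81%.

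The size of the lockdown effect cannot be computed from the document, and no loss of power from it is shown. The point should be settled before adult enrolment closes, but it does not show that the trial will fail.

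**What to change.** 1. In Section 11.1, the synopsis, Section 5.2 and both allocation tables, define the adult target as adults with a valid Day 28 sample. Track it as a blinded pooled count. If control adults are also bled, the pooled count is the per-arm number × 6/2.5: 540 for 225 per arm, 600 for 250, and about 704 for 293.
2. State lockdown losses separately from the 10% dropout allowance.
3. State the power that the chosen count gives under the written 95% interval rule: 84% at 225 analysed per arm, 89% at 250, 94% at about 293. If the original basis of 250 less 10% is kept, replace 94% with about 84%.
4. Replace the age-stratum cells with the revised numbers within 1800, and cross-refer Section 11.1 to the reassignment text.

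**Cost.** Wording in four places, and a running count of Visit 4 samples. The total is unchanged. The downside is fewer children in the descriptive safety strata, which the amendment already accepts. At 2.5:2.5:1, replacing 10 lost Vi-DT samples uses 12 of the 1800 places. Keeping 94% under the written rule would take 326 enrolled per arm, or 326 × 6/2.5 ≈ 783 adults. That leaves about 1,017 places for the two child strata, about 508 each instead of 600, before any lockdown replacement. Keeping 250 less 10% avoids that extra transfer, at the price of the lower stated power.
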